## Compression

### Compression therapy

All groups will have four- or two-layer compression (Profore, Smith and Nephew, UK/Coban, 3M, USA) bandaging applied upon initial review once arterial supply is deemed adequate. All patients will be placed in two-layer bandaging immediately post-procedure which will be replaced with a four-layer bandage within 48 h. Specialist nurses in wound management will subsequently manage compression bandaging in the community with regular review by a vascular surgeon.

## Schedule of events

### Follow-up

All patients will be fully assessed at weeks 6 and 12. Further assessments will be undertaken at 6 and 12 months and annually thereafter. Follow-up will be carried out by assessors blinded to the initial intervention.

### Ulcer assessment

Baseline assessment will be conducted as described in the ‘Randomisation’ section.

The following end-points will be evaluated at each visit:
Integral of the relative ulcer size (area) for each patient over time, standardised to an initial size of 1Duration until complete wound closureAssessment of wound edges Assessment of granulation (BWAT)Assessment of exudation (BWAT)Assessment of wound edges (BWAT)Assessment of undermining (BWAT)Assessment of wound bed tissue (BWAT)Maximum pain in 24 h prior to each visit (0 to 100 VAS)

### Venous clinical severity score

The Venous Clinical Severity Score will be completed at 6 and 12 weeks initially with further assessment at 6- months and annually thereafter until 5-year follow-up is complete.

### EQ5D questionnaire

Quality-of-life will be evaluated by completion of the EQ5D form at 6 weeks and 12 weeks, 6 months and annually thereafter until 5-year follow-up is complete. This data will be further utilised to generate health economic data.

### Healthcare contacts diary

Each participant will be provided with a diary following their venous ablation procedure in order to record all planned and unplanned healthcare contacts (GP visits, public health nurse visits, emergency department visits, hospital admissions, outpatient visits) and ulcer healing data. Community nursing will also report real-time ulcer healing centrally prompting clinical review. The patients will be asked to fill out the diary until their 6-month visit.

### Iliac stent follow-up

Patients who undergo iliac vein stenting alone will undergo follow up iliac vein colour duplex in the radiology department at 1 day, 6 months, 1 year and annually thereafter. Reflux duration, stent patency, stent fracture, in-stent or between stent restenosis will be recorded at each visit. Due to the nature of this surveillance, it will not be possible to blind the ultrasonographer who will not be involved in the trial protocol.

### Superficial venous ablation surveillance

All patients undergoing endovenous ablation will undergo duplex ultrasound assessment of the treated great saphenous vein at 6 weeks and 6 months to assess for recanalisation.

### Crossovers

Any crossovers between treatment groups shall be highlighted and reported in the final report. All patients in the control group with unhealed ulcers will be offered further iliac investigation and treatment where necessary at 6 months. Furthermore, control patients with a history of iliofemoral DVT will be offered investigaton and/or treatment at 3 months due to their higher risk of occlusive disease.

### Withdrawals during follow-up

An individual is free at anytime to withdraw from the trial for any reason without any prejudice as to subsequent therapy. The principal investigator may withdraw and individual from the trial should they be subject to an adverse event whereby it is in the patients best interest to be withdrawn or should they meet any of the exclusion criteria.

### Loss to follow-up

Prior to consent participants will be educated as to the importance and timing of the follow-up protocol. Post-intervention regular patient contact in the community through specialist nurses will allow for a continued patient dialogue regarding follow-up. Should follow-up appointments be missed investigators will endeavour to contact patients by phone or via community liaisons to ensure timely follow-up within the trial protocol. All losses to follow-up and its cause shall be recorded and reported in any trial data.

### Protocol violations

The following will be deemed a violation of protocol and result in removal from the trial
Non-compliance with compression therapy despite adequate patient educationFailure to undergo ablation therapy within 6 weeks

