#### Ulcer assessment

The ulcer will be evaluated by an assessor who has been blinded to the treatment allocation of the patient. Wound size will be calculated using digital planimetry and recorded as cm^2^. Wound assessment will be evaluated using the Bates-Jensen wound assessment tool which has been validated for use in venous leg ulcer assessment [18, 19]. Ulcers that heal prior to intervention will be analysed with intention to treat (Fig. 1).

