## Interventions

### Endovenous ablation and IVUS procedure

All procedures will be carried out by either a vascular surgeon or interventional radiologist with significant experience in both endovenous ablation and IVUS (Visions 0.035, Philips, Amsterdam). The aim is for ablation within 4 weeks of randomisation. All patients will undergo endovenous ablation of refluxing axial superficial veins in the affected leg using thermal or non-thermal ablative techniques under local anaesthesia. Modality of intervention will be at the discretion of the operator. Control procedures will be undertaken in an ambulatory care setting while the interventional group will be managed in an operating theatre or interventional suite. All procedures will be completed under local anaesthesia.

The ablation procedure will be performed simultaneously with IVUS and stenting where applicable. A 9F access sheath will be placed under ultrasound guidance in the saphenous vein at the lowest point of reflux to allow introduction of firstly the IVUS catheter into the ipsilateral common iliac, external iliac and common femoral veins followed by the ablation probe. If the IVUS cannot be passed, the common femoral or jugular vein will be cannulated at the discretion of the operator. Iliac vein interrogation using the IVUS will be undertaken to determine the degree of area luminal area reduction (LAR) at each of the known arterial and ligamentous crossing points on the affected side which predispose to NIVL formation. These include the left and right proximal common iliac veins (where crossed by the right iliac artery), the right and left proximal external iliac vein (where crossed by the external iliac arteries and the retro-inguinal regions.

The LAR will be determined by comparison of the minimal luminal area at the NIVL site to the anatomical minimum for the respective vein, as recommended by experts in the field [22]. Area will be calculated using the standard mathematical formula Area = *A* = *πr*^2^. The reference area values for the iliac veins and the common femoral veins are detailed in Table 1. Lesions will be classified into the degree of stenosis by luminal area as detailed in Table 2.

**Table 1 Tab1:** Normal anatomical reference values for deep veins

Vein	Normal minimum diameter	Normal minimum area
**Common iliac vein**	16 mm	201 mm^2^
**External iliac vein**	14 mm	154 mm^2^
**Common femoral vein**	12 mm	113 cm^2^

**Table 2 Tab2:** Degree of stenosis based on luminal area

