Vein	< 20% stenosis	20 to 49% stenosis	50 to 69% stenosis	> 70% stenosis
**Common iliac vein**	≥ 161mm^2^	160 to 103 mm^2^	102 to 62 mm^2^	≤ 61 mm^2^
**External iliac vein**	≥123mm^2^	122 to 79 mm^2^	78 to 48 mm^2^	≤ 47 mm^2^
**Common femoral vein**	≥ 90 mm^2^	89 to 58 mm^2^	57 to 35 mm^2^	≤ 34 mm^2^

Patients with a stenosis < 50% on the affected side will not have any further iliac or common femoral vein procedure performed. They will undergo endovenous ablation via the previously placed sheath in the great saphenous vein at the knee. Patients with a lesion > 50% will undergo iliac vein stenting with subsequent great saphenous ablation. The venous stent utilised will be at the discretion of the operator to broaden applicability. All residual varicosities shall be treated with foam sclerotherapy using 1% polidocanol. Foam will be standardised with 1:4 polidocanol to air ratio with 2 ml’s administered to each varicosity. Post-operatively those undergoing venous stenting will be placed on a three-month course of a novel oral anticoagulant.

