## Statistical considerations

Once randomisation and intervention is complete, patient outcomes will be assessed using an intention-to-treat analysis. All losses to follow-up at any time-point will be recorded and reported. A research statistician will conduct all analyses independently. Statistical analysis will be conducted using SPSS Version 21 (IBM Corp, Aramonk, NY) The primary feasibility outcome will be reported as the percentage of all eligible patients who agree to participate in the feasibility study. Descriptive data will be provided at baseline and at each follow-up to define variations among and within groups. Continuous data will be presented as mean and standard deviations with confidence intervals of 95%. Categorical data will be reported as frequencies with chi-square or Fischer’s exact *t* test used for comparative data. Where data is not normally distributed, non-parametric tests will be utilised as applicable. Further subgroup and regression analyses will be undertaken to adjust for confounding variables known to affect ulcer healing including age, duration, mobility and size. A *p* value of < 0.05 will be deemed significant.

Contemporary data suggests a median healing time of about 20 weeks for patients with a venous ulcer treated by superficial venous ablation [23]. Assuming a median time to healing in the control arm (those treated with superficial venous ablation and compression alone) of 140 days would be reduced to 110 days by the addition of iliac vein intervention where necessary (i.e. a 20% relative reduction in healing time) would require 270 patients in each arm of the trial, i.e. 540 in total. Allowing for a 10% withdrawal and dropout rate increases the required sample size to 594 patients. In advance of undertaking such a large trial, we aim to undertake a feasibility phase in order to assess eligibility, recruitment rates and provide baseline data for a refined sample size calculation. For this feasibility phase, we aim to recruit 30 patients to each trial arm.

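### Randomised patients are to be removed from the trial, or may be withdrawn, because of post-randomisation events, which contradicts the stated intention-to-treat analysis

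*Protocol article*

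**What the plan says.** Four places in the protocol article bear on who is followed and analysed.

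- **Statistical considerations:** "Once randomisation and intervention is complete, patient outcomes will be assessed using an intention-to-treat analysis".
- **Protocol violations:** "The following will be deemed a violation of protocol and result in removal from the trial". Two events are listed: non-compliance with compression despite education, and failure to have ablation within 6 weeks. The removal is not discretionary.
- **Withdrawals during follow-up:** the principal investigator may withdraw patients after an adverse event, where this is judged to serve their interest, and also "should they meet any of the exclusion criteria". This route is discretionary.
- **Ulcer assessment (under Baseline patient data):** "Ulcers that heal prior to intervention will be analysed with intention to treat".

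No section says that a removed or withdrawn patient continues to be followed or stays in the analysis set. Loss to follow-up says only that losses and their causes are recorded and reported.

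**The concern.** Intention to treat needs every randomised patient to be analysed in the allocated arm, and so needs their outcomes to be collected. A rule that takes patients out because of what happens after randomisation undoes this. If removal means exclusion from the dataset, the analysis is not by intention to treat. If it means only that the patient stops attending, the later outcomes are missing and the analysis cannot be carried out as promised. A separate analysis plan could not repair that, because the data would never have been collected.

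Three things are at stake:

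- the primary efficacy outcome, healing at 3 months;
- the healing data meant to refine the sample size of the definitive trial;
- adverse events and re-interventions after removal, although Primary safety outcomes counts re-intervention without a time limit.

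**Working it through.** **1. The sections side by side.** The violation rule and the analysis rule cannot both be followed. A concrete case is a patient whose ulcer heals after randomisation but before the procedure. Ulcer assessment keeps that patient under intention to treat. If no ablation then follows within 6 weeks, Protocol violations removes the same patient.

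**2. Can removal relate to prognosis or arm?**

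- Compression is part of treatment in both arms, and the Background says it increases healing, so non-compliance is plausibly prognostic.
- The arms are treated in different places: "Control procedures will be undertaken in an ambulatory care setting while the interventional group will be managed in an operating theatre or interventional suite". Waiting times may therefore differ, though the article gives none.
- Randomisation states that there is no sham, so a withdrawal decision need not be blind to allocation.
- "Post-operatively those undergoing venous stenting will be placed on a three-month course of a novel oral anticoagulant". Anticoagulant bleeding and contrast-induced renal injury are listed adverse events. Contraindication to anticoagulation and low eGFR are exclusion criteria. A complication of the added procedure can therefore open the discretionary withdrawal route, by either of its two grounds.

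**3. The plan's own figures.** The medians are 140 and 110 days. Assuming exponential healing, the proportion healed by day t is 1 − 0.5^(t/median). At 91 days:

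- control: 1 − 0.5^(91/140) = 36.3%
- intervention: 1 − 0.5^(91/110) = 43.6%
- planned difference: 7.4 points before rounding

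The same medians give a ratio of 110/140 = 0.786. Schoenfeld's formula at two-sided 5% and 80% power (neither sidedness nor power is stated) then gives the article's 540, if every patient heals. The 594 is 540 × 1.10.

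**4. Illustration of bias with no true effect.** The assumptions, which are not in the article, are that removed patients heal at 15% and that a fraction f of an arm is removed. Overall healing is 36%, from step 3. Healing among those kept is (0.36 − 0.15f)/(1 − f).

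| f removed | Calculation | Healing among those kept |
|---|---|---|
| 0.08 | 0.348/0.92 | 37.8% |
| 0.10 | 0.345/0.90 | 38.3% |
| 0.20 | 0.330/0.80 | 41.3% |
| 0.25 | 0.3225/0.75 | 43.0% |

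The false differences are:

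- 25% v 8%: 43.0 − 37.8 = 5.2 points
- 25% v 10%: 43.0 − 38.3 = 4.7 points
- 20% v 8%: 41.3 − 37.8 = 3.5 points (3.4 before rounding)
- 20% v 10%: 41.3 − 38.3 = 3.0 points (2.9 before rounding)

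The difference favours whichever arm loses more patients. Equal fractions of similar patients give zero. If the removed patients heal better than average, as in the case in step 1, the sign reverses.

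**5. Scale at 30 per arm.** Removing 20-25% is 6 to 7.5 patients; 8-10% is 2.4 to 3. The standard error of the difference at 36% healing is √(2 × 0.36 × 0.64/30) = 12.4 points, so a 5-point bias is about 0.4 standard errors.

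**The case against.** The case against the size of this point is fair in several respects.

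- **Imbalance.** A reader might infer that the 6-week rule will fall more heavily on the intervention arm. The article shows different settings but no waiting times. For outpatients, consent is taken immediately before the procedure and randomisation follows consent. Read literally, that leaves little room for a delay after randomisation, although the aim of ablation within 4 weeks of randomisation implies that a gap can occur. Imbalance is possible, not shown.
- **Direction.** A reader might infer a false benefit for iliac intervention. The removal rates and the 15% are assumed. The only related figure in the article is the 10% allowance for withdrawal and dropout.
- **Harms.** A reader might infer that withdrawal hides complications or biases a safety comparison. The primary safety endpoints are defined within the intervention group. The Safety parameters section requires adverse events to be recorded and reported, so the event that prompts withdrawal should be captured. What can be lost is what happens afterwards.
- **Exclusion criteria.** A reader might say that every ablated patient meets the criterion on previous saphenous intervention. That strains an entry criterion. The natural reading is ineligibility found or arising later, and the withdrawal is discretionary.
- **Feasibility outcomes.** Completion and compliance failures would be noted at the moment of removal. Only later attendance is lost. The primary feasibility outcome, agreement to randomisation among eligible patients, is settled before any removal.

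These points limit the consequences. They leave the contradiction itself untouched, and reporting losses with their causes does not restore the missing outcomes.

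**Conclusion.** The plan is wrong as written. Mandatory removal for two post-randomisation events, together with discretionary withdrawal for others, cannot be combined with the stated intention-to-treat analysis, and the treatment of ulcers healed before the procedure conflicts with the same rule. This conclusion comes from the text and depends on no calculation.

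The size of any bias cannot be derived from the article. Under the assumed rates it is about 3-5 points in either direction, and nil with equal removal of similar patients. That is small against the sampling error at 30 per arm. It is not small against the 7.4 points implied by the planning medians, which is the scale that matters when these data refine the definitive trial. The article does not support a claim that the bias favours the intervention, that the arms will be unbalanced, or that recorded harms would disappear.

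**What to change.** Reconcile Ulcer assessment, Withdrawals during follow-up, Protocol violations and Statistical considerations as follows.

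- In Protocol violations, replace removal with wording to this effect: *these events are protocol deviations; the patient remains in follow-up and is analysed in the allocated arm.*
- In Withdrawals, separate stopping allocated treatment, which stays a clinical judgement and is unchanged, from leaving follow-up, which occurs only when the patient withdraws consent. Once the two are separated, the investigator's grounds for stopping treatment need not be altered.
- In Statistical considerations, state that all randomised patients are analysed as allocated, including those whose ulcers heal before the procedure.
- Report deviations and withdrawals by arm with reasons. Present any per-protocol analysis as sensitivity only.

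The 6-week limit and the compression requirement are matters of clinical conduct and are not questioned here. The cost is protocol wording, modest extra effort to follow non-adherent patients, and a possibly less favourable healing estimate. The sample sizes of 60 and 594 do not change.

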### Premature termination of the study

The trial may be temporarily suspended or prematurely terminated if there is sufficient reasonable cause. Written notification, documenting the reason for trial suspension or termination will be provided to the regional ethical committee and all trial investigators by the principal investigator.

Circumstances that may warrant termination or suspension include, but are not limited to:
Determination of unexpected, significant, or unacceptable risk to participantsDemonstration of efficacy that would warrant stoppingInsufficient compliance to protocol requirementsData that are not sufficiently complete and/or evaluableDetermination of futility

### Schedule of events

The Appendix shows the schedule of events.

## Safety parameters

### Potential adverse events related to intervention

Primary safety endpoints include the need for re-intervention and stent patency. The risk of any significant adverse event occurring is deemed unlikely however all reasonable measures to avoid these events will be undertaken. Any adverse events (as described below) will be recorded and reported in any trial data.
PainBleedingInfectionPhlebitisNerve injury (temporary/permanent)Incomplete ablation of targeted superficial veinRecurrence of ulcerationDeep venous thrombosisPulmonary embolismAdverse reaction to local anaestheticIliac vein injuryFailure of stenting procedurePressure ulceration from dressingsContrast-induced renal injuryStent occlusionBleeding associated with anticoagulation

### Definition of an adverse event

The definition of an adverse event is any untoward medical event related directly or indirectly to an intervention as a result of participation in the trial.

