### Randomisation

Following the consent process randomisation will be undertaken using sequentially numbered opaque sealed envelopes administered by an independent research assistant in the Lambe Institute, University Hospital Galway, allowing for allocation concealment. A unique trial number will be assigned to each individual at the time of randomisation. Patients will be randomised to one of two groups.

Group 1: Compression bandaging and endovascular treatment of saphenous truncal incompetence.

Group 2: Compression bandaging, endovascular treatment of saphenous incompetence with simultaneous iliac vein interrogation with IVUS and stenting if an occlusive lesion > 50% is identified.

A designated member of the research team who will not be involved with data collection will have access to the randomisation data and arrange intervention and investigation as required. There will be no sham intervention.

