### Definition of a serious adverse event

Any event that results in death, a life-threatening adverse event, inpatient hospitalisation or prolongation of existing hospitalisation, a persistent or significant incapacity or substantial disruption of the ability to conduct normal life functions, or a congenital anomaly/birth defect is deemed a serious adverse event.

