### Event reporting

All adverse events will be reported directly to either the site or principal investigator. Recurrent adverse events or serious adverse events in isolation will be reported in turn to the local ethical committee and the risk assessment department for risk analysis. Indications for premature trial cessation are discussed in the ‘Protocol violations’ section.

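### The adverse-event definition requires relatedness to an intervention and the serious-event definition does not, so the two do not nest and unrelated non-serious events have no stated recording commitment

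*Protocol article*

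**What the plan says.** Four consecutive parts of the protocol article's Safety parameters section bear on this.

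- **Potential adverse events related to intervention** gives the recording commitment: "Any adverse events (as described below) will be recorded and reported in any trial data". A list of 16 named events follows directly.
- **Definition of an adverse event** gives the general rule: "any untoward medical event related directly or indirectly to an intervention as a result of participation in the trial".
- **Definition of a serious adverse event** starts: "Any event that results in death, a life-threatening adverse event, inpatient hospitalisation or prolongation of existing hospitalisation". It goes on to incapacity and congenital anomaly. None of this requires relatedness.
- **Event reporting** sets the route: "All adverse events will be reported directly to either the site or principal investigator". Onward reporting is narrower: "Recurrent adverse events or serious adverse events in isolation will be reported in turn to the local ethical committee".

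On blinding, the Randomisation section states "There will be no sham intervention". The section on the ablation and IVUS procedure adds "Control procedures will be undertaken in an ambulatory care setting while the interventional group will be managed in an operating theatre or interventional suite". The Follow-up section states "Follow-up will be carried out by assessors blinded to the initial intervention". The article does not say who judges whether an event is related.

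**The concern.** Relatedness is normally a property recorded about an adverse event. Here it is a condition for being one, so a causal judgement comes before any count. The serious-event definition works the other way and starts from the outcome. A site following both as written would hold a serious-event log containing entries absent from its adverse-event log.

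This matters because the abstract names procedural safety among the primary clinical outcomes, and the secondary objectives include the safety of routine IVUS and/or stenting. Deciding whether a bleed or a thrombosis is related to an intervention usually means knowing which intervention was given. The arms differ visibly: one has IVUS, possibly a stent and, if stented, a course of anticoagulant. The same event could be attributed more readily in one arm than in the other. An event screened out at entry would also not count towards the recurrence that triggers onward reporting of non-serious events, and might be unavailable when the 594-patient trial is planned.

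**Working it through.** The article gives no safety rate, safety sample size or safety power, so there is no figure to reproduce. The check sets the definitions side by side.

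**Step 1. Classify each kind of event under both definitions.**

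| Event | Adverse event? | Serious adverse event? | Result |
|---|---|---|---|
| Related, serious | Yes | Yes | Consistent |
| Unrelated death or hospitalisation | No | Yes | Serious adverse event that is not an adverse event |
| Unrelated, life-threatening only | No | Unclear | That limb reuses the term adverse event, which as defined means related |
| Related, not serious | Yes | No | Recorded, unless the list is closed and omits it |
| Unrelated, not serious | No | No | No stated recording commitment |

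The second row is the contradiction. The third is an unevenness inside the serious-event definition. The fifth is the gap.

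**Step 2. Test the list.** The words pointing below can be read in two ways.

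- *Closed list.* Recording is limited to the 16 items, which conflicts with a definition covering every untoward related event. Stent fracture, for example, is looked for at each stent duplex (Iliac stent follow-up) but is not listed. Residual varicosities receive foam sclerotherapy, but the only drug reaction listed by name is to local anaesthetic.
- *Illustrative list.* The heading calls the events potential, and the pointer may also take in the general definition that follows. The conflict with the list then goes, but the relatedness condition remains.

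The wording needs settling on either reading.

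**Step 3. Subtract what is captured elsewhere regardless of relatedness.**

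- Superficial and deep re-interventions (Re-intervention).
- Ulcer recurrence, and unplanned admission within 6 months (Secondary outcomes).
- All planned and unplanned healthcare contacts until the 6-month visit (Healthcare contacts diary).
- Stent findings in stented patients, at 1 day, 6 months, 1 year and annually (Iliac stent follow-up).
- Recanalisation in all ablated patients, at 6 weeks and 6 months (Superficial venous ablation surveillance).
- Serious events, apart from the unclear life-threatening limb.

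What remains is non-serious events judged unrelated that lead to none of these. The gap is wider after 6 months, when the diary and the admission outcome end but follow-up continues to 5 years.

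**Step 4. Sensitivity of an arm's proportion.** The planned recruitment is 30 per arm. One patient counted or not counted moves the arm's proportion by 1/30 = 3.3 percentage points. This shows leverage only. A bias estimate would need event rates and attribution rates by arm, and the article gives neither.

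**The case against.** The strongest reply has four parts.

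1. *No between-arm adverse-event comparison is specified.* This is correct. The primary safety outcomes are confined to the intervention group, and the statistical section offers only generic tests for categorical data. A reader might infer that a planned safety comparison rests on attribution; the article contains no such plan. What stands is that any tabulation by arm would inherit the entry condition.

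2. *Unblinded causality judgement is not shown.* Also correct. Event reporting says who receives reports, not who assesses their cause, and follow-up assessors are blinded. A reader might take it as established that unblinded investigators decide relatedness; with no sham and visibly different procedures this is possible, even likely, but it is not stated. The full protocol may say who assesses relatedness, and an article's silence on that is not itself a fault. The stated rule that relatedness defines the event is what is open to criticism.

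3. *Unrelated events are not simply lost.* This stands in large part. Thrombosis, pulmonary embolism and bleeding are named in the list and may be recorded by name; the definition reaches indirect relations; and the separate capture is substantial. To say that unrelated events are never recorded or cannot be recovered would go too far. The remaining gap is the narrower one described above.

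4. *This is a convention, and no primary endpoint, sample size or feasibility criterion depends on it.* The second half is fair and limits the weight of the point. The first half does not answer the conflict: two definitions printed one after the other cannot both be applied as a nested pair.

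**Conclusion.** The point holds as an inconsistency in stated rules. The adverse-event definition requires relatedness, the serious-event definition in general does not, and serious adverse events are therefore not a subset of adverse events. The recording list adds a second conflict if it is closed. Non-serious events judged unrelated have no stated recording commitment beyond what other outcomes happen to capture.

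Counts by arm are consequently open to attribution bias. That conclusion rests on the absence of a sham and on relatedness being judged by someone who may know the allocation, which the article neither confirms nor excludes. Neither the direction nor the size of the bias can be derived from the documents, so any numerical example would be invented. The wording should be corrected; the feasibility outcome and the planned sample sizes are unaffected.

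**What to change.** - **Definition of an adverse event:** define it as any untoward medical event in a randomised patient from randomisation onward, whether or not related to an intervention.
- **Relatedness:** record it as a separate field for each event, not as a condition of entry.
- **Potential adverse events related to intervention:** state that the list gives expected events and is not exhaustive.
- **Definition of a serious adverse event:** word it as an adverse event meeting one of the seriousness criteria, so that it is a subset and the life-threatening limb matches the others.
- **Reporting:** tabulate all-cause events by randomised arm, with related events as a supporting table. Procedure-specific items such as stent occlusion or failed stenting should be read as such, since they arise only where stenting is attempted.

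The cost is a change of wording in the protocol and case-report form, plus somewhat more logging of minor, unrelated events in a 60-patient trial. No treatment, visit or sample size changes.
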